### 2.5. Outcomes

The data from the study will be collected through the following instruments and self-assessment questionnaires:Frailty multidimensional screening: SUNFRAIL tool [16];Prescription adherence: medication adherence report scale (MARS) [19];Nutrition: assessment of adherence to the Mediterranean diet (PREDIMED) [20] and mini-nutritional assessment (MNA) [21];Physical activity: short physical performance battery (SPPB) [22];Fall risk: age-friendly environment assessment tool (AFEAT) [23] and time up and go test [24];Cognitive decline: quick mild cognitive impairment (QMCI) [25] and general practitioner assessment of cognition (GPCOG) [26];Loneliness: geriatric depression scale (GDS) [27];Support network: social provisions scale (SPS) [28];Socioeconomic conditions: self-assessment questionnaire (MUSE) [29];Quality of life: SF-12 health survey [30];Usability: system usability scale [31].

The adherence to medical visits will be measured by means of a questionnaire in which older adults will be asked how many times in the last 3 months they visited the GP, received home nursing visits, went to hospital, went to the emergency room, and had specialist examinations, blood tests or other diagnostic examinations. In addition, older adults will be asked whether they have difficulties in making an appointment with the GP or in getting to the GP’s clinic.

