### 2.3. Participants

Each center will independently recruit 100 ambisexuals, randomly selected older adults. Subjects who meet the following inclusion criteria are eligible to participate: age ≥65 years; living at home; accessing participating centers for social and healthcare services other than those covered by this study; and ability to sign the informed consent. Subjects will be excluded if they are <65 years old; residents in care facilities (hospital and nursing home); have overt frailty or disability; are already enrolled in home care; and are unable to understand the study aims and sign the informed consent.

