The availability of older people health data will allow an informed and integrated intervention between local social and health services and the community, with the aim of improving the independent life of older adults, helping them to play an active role in society [34]. The study will have an expected impact on the quality of life of older adults and the improvement of health outcomes in the risk factors of frailty, deriving from participation in collective and individual prevention and health promotion services, such as adapted physical activity programs, primary and secondary nutritional interventions, fall prevention, adherence to drug therapies and medical visits, socialization and psychological support.

The SUNFRAIL+ IT platform makes the pathway more structured and facilitates data collection, especially among citizens in areas with limited access to healthcare services. The availability of an increasing volume of health data on the older adult population will enable healthcare systems to move from reactive disease management to health promotion. The adoption of digital solutions is crucial for the continuous improvement of diagnosis, treatment and personalization of care [35,36]. Frailty screening by means of the SUNFRAIL+ tool will enable the activation of any subsequent diagnostic tests at the relevant healthcare facilities.

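### The adherence-to-medical-visits questionnaire counts contacts with no record of visits due, so it measures healthcare utilisation and access, not adherence

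*Protocol article*

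**What the plan says.** Section 2.5 (Outcomes) of the protocol article introduces the measure with "The adherence to medical visits will be measured by means of a questionnaire". Participants report "how many times in the last 3 months they visited the GP, received home nursing visits, went to hospital, went to the emergency room". The list also takes in whether they "had specialist examinations, blood tests or other diagnostic examinations". Two further items concern access: "older adults will be asked whether they have difficulties in making an appointment with the GP", and whether they have trouble getting to the clinic. No item asks how many visits were scheduled, recommended or due. No scoring rule, total or direction of benefit is stated.

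Section 2.3 (Participants) excludes people who "are already enrolled in home care". Section 2.6 (Statistical Analysis) places paired before–after tests, two-sided at 5%, under the confirmatory analysis. It also enters the parameters measured in the study as explanatory variables in a regression on the SF-12 score. The Discussion mentions "adherence to drug therapies and medical visits, socialization and psychological support" among the services from which benefit is expected.

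The instrument list in Section 2.5 pairs domains with scales. One entry reads "Loneliness: geriatric depression scale (GDS"; another places the short physical performance battery (SPPB) under physical activity.

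**The concern.** Adherence to visits is a proportion: visits attended out of visits that should have taken place. A count of contacts supplies at most part of the numerator. If the result is reported under the label in the article, a change in service use will be presented as a change in patient behaviour.

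The problem is sharpest for hospital and emergency contacts. They sit under the same label as GP visits and tests, yet a rise in them would ordinarily be unfavourable and says nothing about keeping appointments. The programme can also move the planned contacts directly: the Discussion expects screening to lead to further diagnostic tests, so specialist and test counts may rise without anyone attending more of the visits already due.

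At stake are the conclusions about adherence to visits, and the reading of any regression coefficient labelled adherence. A later analysis plan could choose how to group or score the items, but it could not recover a denominator that was never collected.

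**Working it through.** The documents give no visit rates and no calculation for this outcome, so there is no plan figure to reproduce. The one computed figure, 195 subjects for a 10% improvement in the SF-12 (Section 2.6), does not enter here. The check compares what is named with what is collected, with an illustration on assumed values.

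**1. What is collected (Section 2.5).** The contact types are GP, home nursing, hospital, emergency room, specialist, blood tests and other diagnostics: seven counts over three months. There are also two access questions, on making a GP appointment and on reaching the clinic. Visits due: not collected.

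**2. What the label requires.** Let D be visits due, a the proportion of these attended, and U the contacts that were not due (emergency or otherwise unplanned). Adherence is a. The questionnaire observes counts of the form C = D × a + U. With D unknown, a cannot be obtained from C.

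**3. One planned contact type analysed alone (U = 0; D and a assumed).**
- D = 3, a = 0.60: C = 3 × 0.60 = 1.8
- D = 2, a = 0.90: C = 2 × 0.90 = 1.8

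The count is the same although attendance differs by 30 percentage points. The gap therefore does not depend on adding contact types together.

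**4. If contact types were added (all values assumed).**

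| D | a | U | C = D × a + U |
|---|---|---|---|
| 3 | 0.60 | 1.0 | 2.8 |
| 3 | 0.80 | 0.4 | 2.8 |
| 3 | 0.50 | 1.5 | 3.0 |
| 2 | 0.90 | 0.4 | 2.2 |

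From the first row, attendance can rise to 80% with the total unchanged, fall to 50% with the total rising to 3.0, or rise to 90% with the total falling to 2.2. The article does not say that a total will be formed, so this table shows only what would follow if one were.

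**5. Home nursing.** Section 2.3 excludes enrolment in home care, not receipt of a nursing visit in the previous three months. Low baseline use is likely. Since a count cannot go below zero, change from a low baseline is mainly upward. No rate is given from which to size this. Overt frailty and disability are also exclusions, so use may still be low at six months.

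**6. Domain labels.** By its own name, the geriatric depression scale (GDS) measures depression and the SPPB measures physical performance. Section 2.5 lists them under loneliness and physical activity. Sections 2.1 and 2.4 describe a cascade in which answers to the SUNFRAIL tool lead to in-depth scales, so these words may name the domain that triggers the test. Figure 1, which shows the tool, is not reproduced in the text available, so the mapping cannot be checked.

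**The case against.** The strongest reply is that no composite exists. Section 2.5 lists separate questions, states no total and no direction of benefit, and Section 2.6 specifies two-sided tests. Taken item by item, GP use and emergency use are each interpretable, and grouping secondary items is a detail that an article can leave to the full protocol or analysis plan. This stands against any claim that the plan counts more emergency visits as better adherence, which a reader might infer from the shared label but which the text does not say. It does not rescue the label: read item by item, the counts are interpretable as service use, not as adherence.

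The access questions show that the instrument is more than a set of counts. That is correct, but they measure barriers to reaching the GP and not whether due visits were kept.

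A reader might also infer that a significant rise in home nursing is built in by the eligibility rule. The exclusion concerns home-care enrolment and only favours an upward change. Section 2.4 also plans to document how many users the territorial services enrol, so new uptake is something the study sets out to record.

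Nor does the Discussion commit the study to reporting improved adherence or socialization. It lists them as examples of services expected to contribute to quality of life and to outcomes in frailty risk factors.

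Finally, a depression scale is relevant to the psychological distress and psychological support that the Discussion mentions, and a separate scale covers the support network. To say that GDS cannot serve the study's aims would go too far. What remains is narrower: a GDS result should not be reported as a finding on loneliness as such.

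**Conclusion.** The point holds in a limited form. As named in Section 2.5, the outcome cannot be estimated from the items that Section 2.5 describes, because visits due or recommended are not recorded. The data support statements about healthcare utilisation and access. A before–after change in them is not a change in adherence, and hospital and emergency contacts in particular must not be read that way.

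The size cannot be put in trial figures; the numerical examples use assumed values and show only that count and attendance can part company. The before–after reading assumes that the questionnaire is repeated at six months along with the tool and in-depth tests that Section 2.4 names. Low baseline home nursing is likely but not established.

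The effect is confined to outcomes other than the SF-12, which carries the sample size and is the dependent variable of the regression. The GDS and SPPB labels are a minor matter of reporting. The change should be made, but the main analysis does not depend on it.

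**What to change.** - Rename the outcome healthcare utilisation and access, and drop the word adherence for it.
- Report planned contacts (GP, specialist, blood and other diagnostic tests) separately from unplanned contacts (emergency room, hospital). State that a rise in the latter will not be interpreted as better adherence. Keep hospital on its own line, since the item as worded does not separate planned from unplanned admissions.
- Report home nursing separately, with a note that the home-care exclusion favours an upward change.
- Report the two questions on reaching the GP as access.
- Report GDS results as depressive symptoms and SPPB results as physical performance, even if loneliness and physical activity name the SUNFRAIL domain that triggers the test.

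This costs relabelling and splitting one outcome and needs no new data. If a conclusion on adherence is wanted, the number of visits due or recommended in the same three months would have to be collected as well, which is an added data item.

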### 2.6. Statistical Analysis

All complete questionnaires will be analyzed. The statistical analysis will be:(1)Descriptive and exploratory (ADE) with respect to the study population, bringing to light any “features” present in the data;(2)Confirmatory (ADC), focusing on confirming or falsifying the appropriateness of early, integrated and simultaneous care.

For the descriptive analysis, the absolute and relative frequency distributions of all qualitative variables will be calculated, while for the quantitative or semiquantitative variables (e.g., scales from 1 to 10), the main summary and variability indices (mean, median, minimum, maximum, standard deviation, range and interquartile difference) will be calculated.

The main statistical tests will be used for confirmatory analyses, depending on the types of variables: chi-square test, McNemar test for dichotomous data, parametric t-test and Wilcoxon’s nonparametric test for paired data (before–after). All tests will be two-sided, with a 5% significance level. The multiple linear regression model will be used to examine the contribution of the parameters measured during the study (explanatory variables) on the quality of life (score measured by the SF-12 questionnaire, dependent variable).

The analyses will be performed using IBM SPSS Statistics software for Windows, version 26, Armonk, NY, USA, IBM Corp.

With a type 1 error of 5% and a study power of 80%, accepting a 95% confidence level and targeting an improvement of 10% in the SF12 score, the requested sample size will be composed of 195 subjects. The number of 700 clients exceeds the needed number of participants, which can be useful to perform nested analysis.

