### Strengths and Limitations

One of the strengths of the study is the participation of several centers, providing different services but all interacting with the target population along the SUNFRAIL specific domains. This will make it possible to demonstrate that the identification of risk factors for frailty in older adults and their enrolment in prevention and health promotion services should not only take place at a dedicated healthcare facility but in different settings and at different levels of care.

The main limitation of the study is that the intervention strategies of the health systems involved and the services available from health organizations are not uniform. This does not allow the study to be able to investigate the effectiveness of prevention and health promotion interventions to be linked to the screening of frailty risk factors. The exploitation of the study outcomes depends very much on the ability of the centers to link the screening of frailty’s risk factors with the services currently available in the participating centers for prevention and health promotion.

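### The statement that 700 participants are more than enough holds, for conclusions beyond these seven centres, only if SF-12 change is very weakly correlated within centre

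*Protocol article*

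**What the plan says.** All of this is in the protocol article.

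- **Design.** The Abstract gives seven centres in seven Italian regions. Section 2.3 (Participants) says "Each center will independently recruit 100" older adults, so the 700 are seven groups of 100.
- **Sample size.** Section 2.6 (Statistical Analysis) fixes a 5% type I error and 80% power and continues: "targeting an improvement of 10% in the SF12 score, the requested sample size will be composed of 195 subjects". It then adds: "The number of 700 clients exceeds the needed number of participants, which can be useful to perform nested analysis". No ICC, design effect or allowance for incomplete data accompanies either figure, and only complete questionnaires are to be analysed.
- **Tests.** The same section lists chi-square, McNemar, paired t and Wilcoxon tests for the confirmatory before–after comparisons, and a multiple linear regression with SF-12 as the outcome. It states: "All tests will be two-sided, with a 5% significance level". Centre is not mentioned.
- **Differences between centres.** Strengths and Limitations gives as the main limitation that "the intervention strategies of the health systems involved and the services available from health organizations are not uniform".
- **Reach of the conclusion.** Section 4 (Conclusions) calls the study nationwide and says that it aims to demonstrate the effectiveness of the approach.

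**The concern.** Each centre recruits on its own and offers its own services, and Section 2.4 (Intervention) includes group activities. Six-month change in SF-12 may therefore differ systematically between centres. If it does, and the result is read as applying to centres in general, 700 people carry less information than 700 independent observations.

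Two statements are then affected. The first is the 5% level of the named tests: their standard errors would be too small, and a pooled before–after change could be declared significant too often. The second is the claim of spare sample size for nested analyses, which may shrink or disappear. In the regression, centre is also a possible confounder, since both the services offered and the outcome may vary with it.

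**Working it through.** **Inputs from the article.** Two-sided alpha 0.05, power 0.80, stated need 195, planned total 700, seven centres, m = 100 per centre.

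**Inputs that are assumed.** The ICC of SF-12 *change*, written ρ, shown at 0.01, 0.02 and 0.05; and the share of incomplete data, shown at 0 to 30%. The article gives neither.

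**Step 1: the stated 195.** It cannot be reproduced, because a 10% improvement needs a baseline mean and an SD of change, and neither is given. Working backwards with the one-sample (paired) formula n = ((z₀.₉₇₅ + z₀.₈₀)/d)²:

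- 195 implies d = (1.960 + 0.842)/√195 = 0.2006.
- d = 0.20 gives 196.2, so 197, or 199 with the t distribution.

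So 195 is close to an independent-subjects paired calculation at a standardised change of about 0.20, but it cannot be shown to come from one. The steps below take 195 at face value.

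**Step 2: design effect.** DE = 1 + (m − 1)ρ = 1 + 99ρ. Effective n = 700/DE. Total needed = 195 × DE.

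**Step 3: type I error of an unadjusted paired t-test with random centres.** Approximately 2 × (1 − Φ(1.96/√DE)).

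**Step 4: power when the analysis respects seven centres.** Noncentral t with 6 df and noncentrality 0.2006 × √(effective n).

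| ICC of change | DE | Effective n | Total needed | Unadjusted type I error | Power, 6 df |
|---|---|---|---|---|---|
| 0.01 | 1.99 | 352 | 389 | 16.5% | 0.88 |
| 0.02 | 2.98 | 235 | 582 | 25.6% | 0.73 |
| 0.026 | 3.57 | 196 | 697 | 30.0% | 0.65 |
| 0.05 | 5.95 | 118 | 1,161 | 42.2% | 0.45 |

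A simulation of 20,000 trials with random centre effects agrees. The unadjusted paired t-test rejected in 5.0%, 16.8%, 30.3% and 42.9% of trials at an ICC of 0, 0.01, 0.026 and 0.05. A t-test on the seven centre means stayed between 5.0% and 5.2%.

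**Step 5: break-even ICC.**

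- Simple formula: (700/195 − 1)/99 = 0.0262.
- With 10%, 20% or 30% incomplete data: 0.025, 0.024 or 0.022. For example, at 20%, (560/195 − 1)/79 = 0.0237.
- With 6 df: power equals 0.80 at an ICC of about 0.015.

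The two thresholds differ because the simple formula uses a normal approximation and ignores that only seven centres estimate the between-centre variation.

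**The case against.** **Centres as fixed.** The seven centres are not described as a sample from a wider population. If inference is limited to them, the paired-test inflation does not apply. This stands, and it is why the point is conditional. The nationwide aim of demonstrating effectiveness nevertheless points to a wider reading, and the article does not say which is meant.

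**No ICC is given, and the relevant one may be small.** What matters is the correlation of change, and stable differences in SF-12 level between centres cancel in a before–after difference. Differing case mix alone therefore does not imply a large value. This stands too: non-uniform services give a reason to expect some correlation, but no size.

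**A condensed article may leave centre to the analysis plan.** The regression's explanatory variables are left open, and nested analysis is not defined. A reader might infer that the study will ignore centre in every analysis. The article does not support that, and the missing covariate alone would be no finding. What remains is a statement the article does make: that 700 exceeds the need, without condition, beside named tests that assume independence.

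**The limitation is acknowledged.** The article says that non-uniform services prevent it from investigating the effectiveness of the linked interventions. This narrows what the regression can claim and softens the confounding argument. It does not bear on the standard errors or on the sufficiency statement.

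**Conclusion.** The point holds in conditional form. For conclusions beyond these seven centres, the sufficiency statement and the 5% level both require a small ICC of SF-12 change: at most about 0.015 to keep 80% power with seven random centres, or 0.026 by the simple formula. The 5% level is affected earlier than the sample size. At an ICC of 0.01 the 700 are still enough, yet the unadjusted paired t-test already has about three times its nominal error.

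The result rests on three assumptions: an ICC that the article does not give, inference to a wider set of centres, and the stated 195, which cannot be verified. A smaller true need would raise both thresholds; a larger one would lower them.

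Two stronger readings are tempting and are not supported. One is that 700 is too few: nothing in the article shows that the ICC exceeds either threshold. The other is that 195 is known to be an independent-subjects figure: it is consistent with one, no more.

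**What to change.** 1. Include centre as a fixed effect in the SF-12 regression.
2. Report the six-month change for each centre, with a test of heterogeneity.
3. For the pooled change, either use a centre-aware analysis (a t-test on centre means, or a mixed model with random centre and small-sample degrees of freedom) or state that inference is limited to these seven centres.
4. Replace the sufficiency sentence with, for example: *195 assumes independent participants; for inference beyond these centres, 700 (100 per centre) keeps 80% power only if the ICC of SF-12 change is at most about 0.015 with seven centres analysed as random (0.026 by the simple design-effect formula), before any allowance for incomplete data.*
5. State the baseline mean and the SD of change behind 195, so that the figure can be checked.

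No extra recruitment or data collection is needed. The cost is a change of analysis wording, wider intervals and a less favourable sample-size statement.

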### 2.7. Ethics Statement

Each center is responsible for conducting the study in accordance with good clinical practice and international quality standards for the design, conduct and dissemination of studies involving human subjects [32]. The study protocol, informed consent and any accompanying material provided to the patient have been approved by the local Ethics Committee of Università “Federico II”–Azienda Ospedaliera di Rilievo Nazionale “A. Cardarelli” (record number: 284/22). The research protocol was registered at ClinicalTrials.gov on 9 December 2022 (registration number: NCT05646472).

